***Psychosis Measures***

### Positive and Negative Syndrome Scale (PANSS)

The PANSS is a 30-item therapist-rated scale used to evaluate the symptoms of schizophrenia. All 30 items are rated on a 7-point scale (1 = absent; 2 = minimal; 3 = mild; 4 = moderate; 5 = moderate severe; 6 = severe; 7 = extreme) that will be combined to form five subscales: a) Positive Symptoms (P1 Delusions, G9 Unusual thought content, P3 Hallucinatory behaviour, P6 Suspiciousness and persecution, P5 Grandiosity), b) Negative Symptoms (N2 Emotional withdrawal, N1 Blunted affect, N4 Passive apathetic social withdrawal, N6 Lack of spontaneity, N3 Poor rapport, G7 Motor retardation, G16 Active social avoidance), c) Disorganization often termed Cognitive (P2 Conceptual disorganization, G11 Poor attention, N5 Difficulty in abstract thinking, G13 Disturbance of volition, N7 Stereotyped thinking, G5 Mannerisms/posturing, G15 Preoccupation, G10 Disorientation), d) Affect often termed Depression-Anxiety (G2 Anxiety, G6 Depression, G3 Guilt feelings, G4 Tension, G1 Somatic concern) and e) Resistance or Excitement/Activity (P7 Hostility, G14 Poor impulse control, P4 Excitement, G8 Uncooperativeness) [7].

The items will also be combined to obtain a PANSS Total Score that can also be used to measure and categorise illness severity [8].

**Scoring:** The five subscales are scored by adding up the corresponding items within each subscale, which will produce subscale scores ranging from 4 to 28, 5 to 35, 7 to 49 and 8 to 56 for the resistance, positive symptoms and affective, negative symptoms and disorganisation subscales respectively, with higher scores indicating more severe symptoms.

The PANSS Total Score is obtained by adding up the 30 items producing a score ranging from 30 to 210, with higher scores indicating more severe symptoms. PANSS baseline total scores between 58 and 74 corresponds to "mildly ill", between 75 and 94 to "moderately ill", between 95 and 115 to "markedly ill" and between 116 and 210 to severely ill. (NB We did not set an “illness” criteria for entry to trial but in relation to PANSS, to be experiencing at least mild hallucinations or delusions symptoms – scoring a 3 on P1 or P3 on PANSS – see inclusion criteria).

An improvement score will also be computed for 16-week and 28-week outcomes using the formula [9]:

$$\frac{{(PANSS}_{baselinetotalscore}-{PANSS}_{endpointtotalscore}) x 100}{\left( {PANSS}_{baselinetotalscore}-30 \right)}$$

**Missing items:** Missing items within subscales will be imputed using a mean of the completed items if no more than 35% items within each subscale are missing; no more than 2 missing item for the negative symptoms and disorganisation subscales and 1 missing item for the positive symptoms, affect and resistance subscales.

### Psychotic Symptom Rating Scales (PSYRATS)

The PSYRATS is a 17-item therapist-administered instrument designed to quantify the severity of delusions and hallucinations, each item being rated from 0 (absent) to 4 (severe).

The PSYRATS has 2 subscales: the auditory hallucinations subscale (AHS) consisting of 11 items (i.e., Frequency, Duration, Location, Loudness, Beliefs Re: Origin, Amount of negative content of voices, Degree of negative content, Amount of distress, Intensity of distress, Disruption to life caused by voices and Controllability of voices) and the delusions subscale (DS) consisting of 6 items (i.e., Amount of preoccupation, Duration of preoccupation, Conviction, Amount of Distress, Intensity of Distress and Disruption) [10].

**Scoring:** Each of the subscales are scored by adding up the items within each subscale, which will yield a score ranging from 0 to 44 for the AHS subscale and from 0 to 24 for the DS, with higher scores indicating higher severity of hallucinations and delusions respectively.

**Missing items:** Missing items within subscales will be imputed using a mean of the completed items if no more than 35% items within each subscale are missing (i.e., 3 and 2 missing items for the AHS and DS subscales respectively).

### Questionnaire about the Process of Recovery (QPR)

The QPR is a 15-item self-reported measure of personal recovery. Each item is scored using a 5-point Likert scale ranging from 0 (disagree strongly) to 4 (agree strongly) [11].

**Scoring:** A total score ranging from 0 to 60 is obtained by summing all the items, with high scores indicating better progress towards recovery goals.

**Missing items:** Missing items will be imputed using a mean of the completed items if no more than 35% items (i.e. 5 items) are missing.

***Imagery***

### Mental Imagery in Psychosis Questionnaire/Visual Analogue Scales (MIPQ/VAS)

The MIPQ is an instrument used to measure mental imagery. For each image, the participants will complete 7 items rated on a visual analogue scale ranging from 1=not at all to 10=extremely [12].

**Scoring:** A total score ranging from 7 to 50 is obtained by summing items 1 to 5, with higher scores indicating more problematic imagery. Items 6 and 7 will be reported separately.

**Missing items:** Missing items 1 to 5 will be imputed using a mean of the completed items if no more than 1 item is missing (i.e., 35% items).

### Psychosis Imagery Questionnaire (PIQ)

This tool is not a secondary outcome for iMAPS-2. Validation of the new measure will be performed after the trial is completed, analysis and results of the validation study will be reported elsewhere.

***Schemas***

### Brief Core Schema Scale (BCSS)

The BCSS aims to provide a theoretically coherent self-report assessment of schemata concerning self and others in psychosis. It consists of 24 items concerning beliefs about the self and others that are assessed on a 4-point Likert scale (Believe it: 1=slightly, 2=moderately, 3=very much and 4=totally). Four domains are obtained: negative-self (items 1 to 6), positive-self (items 7 to 12), negative-others (items 13 to 18) and positive-others (items 19 to 24). The participant is asked to indicate in a dichotomous No/Yes format whether they held each belief. Then, if they held the belief (i.e. answered yes), they are asked to indicate their degree of belief conviction by circling a number from 1 to 4. If they do not hold the belief, a score of zero is assigned [13].

**Scoring:** Each domain is scored by adding the items within each domain, which will yield a score ranging from 0 to 24 with higher scores indicating higher negative/positive evaluation of self/others.

**Missing items:** Missing items within domains will be imputed using a mean of the completed items if no more than 35% items within each domain are missing (i.e., 2 missing items).

***Trauma***

### International Trauma Questionnaire (ITQ)

The ITQ is an 18-item self-report measure with each item rated on a 5-point Likert scale ranging from 0 (Not at all) to 4 (Extremely) focusing on the core features of Post-Traumatic Stress Disorder (PTSD) and Complex PTSD (CPTSD). The ITQ has two major subscales with three symptom clusters in each:

1. Post-Traumatic Stress Disorder (PTSD); Re-experiencing, Avoidance AND Sense of threat.
2. Disturbances in self-organization (DSO); Affective dysregulation, Negative self-concept and Disturbances in relationships.

The PTSD and DSO symptoms are accompanied by three items measuring associated functional impairments in the domains of social, occupation, and other important areas of life [14].

**Scoring:** There are two components of scoring and interpretation for this tool; Categorical scoring for the diagnosis of PTSD and CPTSD, and a dimensional component which measures symptom severity. iMAPS-2 is concerned with the dimensional component only.

The PTSD (items 1 to 6) and DSO (items 10 to 15) subscales range from 0 to 24 and they are computed by summing the items within each subscale, with higher scores indicating more severe symptoms. A total score for CPTSD ranging from 0 to 48 can be obtained by summing the 12 items comprising the PTSD and DSO subscales, with higher scores indicating more severe symptoms.

**Missing items:** Missing items for the PTSD and DSO subscales will be imputed using a mean of the completed items within each subscale if no more than 35% items are missing (i.e., 2 items per subscale). A total score for CPTSD will only be computed if there are valid scores for PTSD and DSO subscales, after item imputation if necessary.

### Basic Emotions Scale (BES)

The BES is a self-report measure comprising 20 items each rated on a 7-point Likert scale ranging from 1 (never) to 7 (very often) that can be combined to form 5 subscales: anger (items 1, 6, 11 and 16), sadness (items 2, 7, 12 and 17), disgust (items 3, 8, 13 and 18), anxiety (items 4, 9, 14 and 19), and happiness (items 5, 10, 15 and 20).

**Scoring:** Each subscale is obtained by summing their corresponding item scores which yield subscales ranging from 4 to 28 with higher scores indicating higher frequency of emotions experienced [15].

**Missing items:** Missing items within subscales will be imputed using the mean of the completed items in each subscale, if no more than 35% of the items (i.e.,1 item) within each subscale are missing.

***Mental Health and Functioning***

### Beck Anxiety Inventory (BAI)

The BAI is a 21-item self-report instrument in which patients rate their experience of the severity of each symptom of anxiety. Each items is rated on a 4-point Likert scale with the anchors of 0 (Not at All) to 3 (Severe) [16].

**Scoring:** A total score, ranging from 0 to 63, is obtained by adding each of the item scores, with higher scores indicating higher levels of anxiety.

**Missing items:** Missing items will be imputed using a mean of the completed items if no more than 35% items (i.e. 7 items) are missing.

### Calgary Depression Scale (CDSS)

The CDSS is a 9-item clinician rated outcome measure that assesses the level of depression in people with schizophrenia. Each item is rated on 3-point Likert-scale (0 = absent; 1 = mild; 2 = moderate; 3 = severe) [17].

**Scoring:** A total score, ranging from 0 to 27, is obtained by adding each of the item scores, with higher scores indicating higher levels of depression.

**Missing items:** Missing items will be imputed using a mean of the completed items if no more than 35% items (i.e. 3 items) are missing.

### Warwick Edinburgh Mental Well Being Scale (WEMWBS)

WEMWBS is a self-reported instrument measuring subjective well-being focusing entirely on positive aspects of mental health. It is composed of 14-items each rated on 5-point Likert scale (1 = none of the time; 2 = rarely; 3 = some of the time; 4 = often; 5 = all of the time) [18].

**Scoring:** A total score ranging from 14 to 70 is obtained by summing the item responses of all 14 items, with higher scores indicating greater positive mental wellbeing.

**Missing items:** Missing items will be imputed using a mean of the completed items if no more than 35% items (i.e. 4 items) are missing.

### The Personal and Social Performance Scale (PSP)

The PSP is a therapist-reported instrument evaluating the degree of difficulty a participant exhibits over a 1-month period in four domains: (a) personal and social relationships; (b) socially useful activities, including work and study; (c) self-care; and (d) disturbing and aggressive behaviours. The patient’s degree of severity in the four domains is rated on a six-point scale from absent (which means no problems on this dimension) over mild, manifest, marked, severe to very severe difficulties in the given area.

[19].

**Scoring:** Out of the ratings on the four domains, a total score on a 100-point scale is computed by the therapist according to manual instructions, with higher scores indicating better personal and social functioning.

**Missing items:** Due to the nature of the PSP scoring is not feasible to impute missing domains to obtain a total score. If a participant declines to answer part of the interview relating to a particular domain, then the PSS will not be scored.

### Working Alliance Inventory Short form (WAI-SR)

This is a rating scale designed to measure the working alliance between therapists and their clients during therapy sessions. The client version is composed of 12 items each rated on a 5-point Likert scale (1 = Seldom; 2 =Sometimes; 3 = Fairly often; 4 = Very often; 5 = Always) on three domains: a) Goal: client and therapist agree on goals of treatment (items 4, 6, 8 and 11), b) Task: whether they agree on how to achieve those goals (items 1, 2, 10 and 12) and c) Bond: whether they will be able to or have already established a personal bond with each other (items 3, 5, 7 and 9).

The therapist version is composed of 10 items also rated on a 1-5 point scale on 3 domains: Goal (items 3, 6 and 8), Task (1, 4 and 10) and Bond subscales (2, 5, 7 and 9).

**Scoring:** A total score is obtained be adding all 12 items producing a scale ranging from 12 to 60, with higher scores indicating greater alliance in the client version.

For the therapist version a total score is obtained be adding all 10 items producing a scale ranging from 10 to 50 with higher scores indicating greater alliance.

**Missing items:** Missing items within domains will be imputed using the mean of the completed items in each domain, if no more than 35% of the items (i.e.,1 item) within each domain are missing for the client and therapist versions. A total score will be computed, for the client and therapist versions, if no more than 1 missing item per domain is missing.

***Adverse Effects***

### Clinical Global Impression- Improvement (CGI-I)

The CGI I is a stand-alone measure rating the change from baseline to treatment. The CGI I is rated on a 7-point scale: 1=very much improved since the initiation of treatment; 2=much improved; 3=minimally improved; 4=no change from baseline (the initiation of treatment); 5=minimally worse; 6= much worse; 7=very much worse since the initiation of treatment [20].

Participant and therapist versions will be reported separately.

### Clinical Global Impression - Severity (CGI-S) Version

The CGI S is a stand-alone measure rating illness severity. The CGI S is rated on a 7-point scale: 1=normal, not at all ill; 2=borderline mentally ill; 3=mildly ill; 4=moderately ill; 5=markedly ill; 6=severely ill; 7=among the most extremely ill patients [20].

Participant and therapist versions will be reported separately.

## Analysis methods

**Objective 1.** What number and percentage of eligible patients/service users consent to the trial (recruitment)?

**Outcomes**

- Number of patients referred to the study.
- Number of patients (potential participants) contacted
- Number of patients screened for eligibility.
- Number of patients screened but not eligible, along with reasons for non-eligibility or withdrawal of interest.
- Number of eligible patients.
- Number of eligible patients not recruited, along with reasons for non-recruitment
- Number of participants recruited (consented).
- Source of recruitment
- Number of participants randomised.

**Analysis**

The number of people screened, eligible, consented and randomised will be summarised and reported in a CONSORT flow diagram (see section 6).

Randomisation rates to assess the progression criteria to conduct a definitive trial will be presented as point estimates with (exact binomial) 95% confidence intervals.

Monthly randomisation rates will also be presented overall and tabulated by randomised group as stated in section 6.3

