## Study Setting

**Setting:** NHS Early Intervention (EI) in Psychosis and Community Mental Health Team services, including inpatient wards Pennine Care NHS Foundation Trust (Greater Manchester). Forty-five participants will be recruited in Pennine Care NHS FT (30 in the iMAPS plus usual care arm and 15 in the usual care arm). The recruitment rate will be five participants per month, for approximately nine months.

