## Eligibility CRITERIA

**Inclusion Criteria**

**Participants:**

1. Meeting criteria for a schizophrenia-spectrum diagnosis (ICD-10 codes F20, F22, F23, F25, F28, F29; ICD-11 codes F20, F22, F23, F25, F28, F29; ICD-11 codes 6A20, 6A21, 6A23, 6A24, 6A2Y,6A2Z) AND Score of 3 Mild or above on P1 Delusions or P3 Hallucinations on Positive and Negative Syndrome Scales (PANSS).

**Or**

a criterion level of positive symptoms severity indicated by a score of > 3 (mild symptom present) on either the delusions (P1), hallucinations (P3), grandiosity (P5) or suspiciousness (P6) items of the PANSS in the previous week (this is usually the operational criteria to under the care of early intervention psychosis team)

And/or the psychosis transition criteria of the CAARMS

1. aged 16 and above
2. Identifying a distressing image^[[1]](#footnote-1)^ (Rated 50% distressing or above) related to the psychotic experience scoring 3 or above on PANSS. The participant will self-report the image as distressing (e.g. Have you had a distressing image over the past month? Yes/No What would you rate the distress over the past month from 0-100?.
3. capacity to give informed consent,
4. under the care of an NHS mental health team the study is recruiting from
5. with a keyworker/access to a duty team worker.

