**Additional Tables**

**Monthly and cumulative randomisation**

We were interested in the number and percentage of eligible patients/service users consenting to the trial (recruitment).

Participant recruitment began on 14^th^ July 2022 and the final participant was randomised on 08^th^ September 2023. The study recruited its target of 45 participants randomised, 100%, 95%CI (92% to 100%) and therefore met the green criteria for recruitment. Monthly and cumulative randomised figures are shown in the table below. The overall average monthly rate randomised was 45/15 = 3 participants per month.

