**Supplementary Table 11: CONSORT Combined reporting checklist**

| **Section** | **CONSORT-PILOT** | **Pp.** | **CONSORT-SPI** | **Pp.** |
| --- | --- | --- | --- | --- |
| **Title and abstract** |  |  |  |  |
| Title | 1a.Identification as a pilot or feasibility randomised trial in the title | 1 |  |  |
| Abstract | 1b. Structured summary of pilot trial, design, methods, results and conclusions (see CONSORT abstract extension for pilot trials) | 2 | 1b.Refer to CONSORT extension for social and psychological intervention trial abstracts | 2 |
| **Introduction** |  |  |  |  |
| Background and rationale | 2a. Scientific background and explanation of rationale for future definitive trial, and reasons for randomised pilot trial | 3 | 2b. If pre-specified, how the intervention was hypothesised to work. | 3 |
| Objectives | 2b. Specific objectives or research questions for pilot trial | 7 |  |  |
| **Methods** |  |  |  |  |
| Trial design | 3a. Description of pilot trial design (such as parallel, factorial) including allocation ratio | 4 |  |  |
|  | 3b. Important changes to methods after pilot trial commencement (such as eligibility), with reasons | N/A |  |  |
| Participants | 4a. Eligibility criteria 4 for participants | 4 |  |  |
|  | 4b. Settings and locations where the data were collected | 4 |  |  |
|  | 4c. How participants were identified and consented | 4 | 4a. Where applicable, eligibility criteria for settings and those delivering the interventions. | 4 |
| Interventions | 5.The interventions for each group with sufficient details to allow replications, including how and when they were actually administered | 6 | 5a. Extent to which interventions were actually delivered by providers and taken up by participants as planned. | 12 |
|  |  |  | 5b Where other informational materials about delivering the intervention can be accessed. | 6 |
|  |  |  | 5c Where applicable, how intervention providers were assigned to each group | N/A |
| Outcomes | 6a. Completely defined prespecified assessments or measurements to address each pilot trial objective specified in 2b, including how and when they were assessed | 7 |  |  |
|  | 6b. Any changes to pilot trial assessments or measurements after the pilot trial commenced, with reasons | N/A |  |  |
|  | 6c. If applicable, prespecified criteria used to judge whether, or how, to proceed with future definitive trial | 7 |  |  |
| Sample size | 7a. Rationale for numbers in the pilot trial | 5 |  |  |

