**Supplementary Table 12: Changes and Amendments submitted for Research Ethics Committee (REC) approval**

|  | **Description** | **Date** |
| --- | --- | --- |
| 1 | Three primary feasibility outcomes were included in the HRA approved Protocol. At trial registration, two additional outcomes were listed: therapy safety (AEs and SAEs) was added and blinding breaks. This was an administrative error (both therapy safety and blinding breaks were mentioned in the protocol and are reported in this outcomes manuscript). | 22/05/2022 |
| 2 | **Substantial Amendment**  1. Reduce Inclusion Criteria Age Range from 18 years to 16 years old, to expand access to a greater number of Early Intervention Psychosis service users/patients.  2. Expand recruitment to include adult inpatient wards, for patients who are judged to have capacity to consent as assessed by a key clinician, to expand access to the study for potentially eligible service users/patients.  3. To capture imagery characteristics each therapy session, as a potential mechanism of change  4. Seek verbal consent to document demographics at screening stage, to record any differences between those screened and those eventually randomised, to support maximising purposive sampling of participants from different ethnic minority backgrounds. | 21/11/2022 |
| 3 | **Substantial Amendment**  Substantial Amendment requested to add a third qualitative study. The aim of the study is explore therapist's experiences of delivering imagery focused therapy through interviews and to amend participant’s qualitative interview schedule. | 20/01/2023 |
| 4 | **Non-Substantial Amendment**  Non-Substantial Amendment to extend study end date to 30^th^ June 2024, to allow 16 week and 28-week assessments to be completed. Recruitment window had been extended due to research assistants leaving post and new colleagues appointed, CI bereavement leave, and delays in contacting wider mental health team for referrals due to MH team staff absences due to Flu season/Ill Health in Winter 2022/23 during recruitment phase. | 27/10/2023 |

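### Eligibility was widened during recruitment, but the Objective 1 screening, eligibility and consent counts are planned as single totals; the reported average of 3 randomised per month also counts 13.9 elapsed months as 15

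*Combined protocol and SAP*

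**What the plan says.** **Eligibility.** Supplementary Table 12, item 2, dated 21/11/2022, lists two changes that widen entry: "Reduce Inclusion Criteria Age Range from 18 years to 16 years old" and "Expand recruitment to include adult inpatient wards". Both are in the current protocol. Its Eligibility Criteria read "aged 16 and above", and its Study Setting describes services "including inpatient wards Pennine Care NHS Foundation Trust". The supplement dates the recruitment period: "Participant recruitment began on 14^th^ July 2022 and the final participant was randomised on 08^th^ September 2023".

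**Counts.** Research question 1 asks how many eligible patients consent, as a number and a percentage. SHEAP 6.1 and SHEAP 7.2, Objective 1 list referred, contacted, screened, eligible, consented and randomised patients, each as one total for the CONSORT diagram. The SHEAP does not mention the amendment.

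**Rates.** For randomisation the SHEAP goes further: "Monthly randomisation rates will also be presented overall and tabulated by randomised group". Supplementary Table 1 then gives the number randomised in each calendar month. The text above that table adds one summary figure: "The overall average monthly rate randomised was 45/15 = 3 participants per month".

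**Reporting.** In the CONSORT checklist (Supplementary Table 11) the item on changes after the start is completed as "3b. Important changes to methods after pilot trial commencement (such as eligibility), with reasons | N/A".

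**The concern.** Until the amendment took effect, a 17-year-old or a ward patient was ineligible; afterwards the same person could be eligible. The denominator of research question 1 therefore changed meaning part-way through, and one pooled percentage does not say which definition it describes. A team planning the definitive trial would want to know how the screening and consent figures behaved under the criteria now in the protocol, and how many participants came in through the added routes.

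The average monthly rate is a second, independent matter. Recruitment opened in mid-July and closed on 8 September, so the first and last rows of the monthly table are part months. Dividing by 15 rows lengthens the period and lowers a stated feasibility figure.

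The N/A at CONSORT item 3b conflicts with Supplementary Table 12 whatever the size of the other two.

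**Working it through.** **Inputs.** Monthly randomisations from Supplementary Table 1: Jul-22 to Sep-23 = 0, 1, 0, 2, 5, 3, 4, 6, 3, 5, 5, 3, 1, 3, 4. Start and end dates are from the text above that table. The amendment date is from Supplementary Table 12. One month is taken as 30.44 days.

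**1. The reported figures.** The rows sum to 45, there are 15 rows, and 45/15 = 3.0 per month. The exact 95% interval for 45 of 45 has lower limit 0.025^(1/45) = 0.921, that is 92% to 100%. Both figures reproduce.

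**2. The rate over elapsed time.** Counting both end dates, 14 July to 20 November 2022 is 130 days and 21 November 2022 to 8 September 2023 is 292 days. The total is 422 days, and 422/30.44 = 13.9 months. The rate is 45/13.86 = 3.25 per month. The July row covers 18 days and the September 2023 row 8 days, which accounts for the difference from 15.

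**3. How far the monthly series can be split.** July to October sums to 3, November is 5, and December to September sums to 37. The five November randomisations cannot be dated, so a cut at 21 November gives a range:

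| Allocation of the November five | Before (130 days, 4.27 months) | After (292 days, 9.59 months) |
|---|---|---|
| all before | 8/4.27 = 1.9 per month | 37/9.59 = 3.9 per month |
| all after | 3/4.27 = 0.7 per month | 42/9.59 = 4.4 per month |

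**4. Whether the difference reflects the criteria.** Only 1 participant was randomised from 14 July to the end of September. Setting those opening months aside:

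- October and November: (2 + 5)/2 = 3.5 per month.
- 1 December to 8 September (282 days, 9.26 months): 37/9.26 = 4.0 per month.
- Under a constant rate from October, 44 randomisations over 2 + 9.26 = 11.26 months would put 44 × 2/11.26 = 7.8 in October and November; 7 were seen.

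If the amendment took effect only from February 2023 (an assumption), October to January gives (2 + 5 + 3 + 4)/4 = 3.5 per month. From 1 February to 8 September (220 days, 7.23 months) the rate is 30/7.23 = 4.15. On either cut, little of a step remains once start-up is removed.

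**5. The percentage consenting.** Write e1 and c1 for eligible and consenting patients before the change, and e2 and c2 for those after it. The pooled figure is (c1 + c2)/(e1 + e2), an average of c1/e1 and c2/e2 weighted by e1 and e2, with e2 counted under the wider definition. None of the four counts is in the readable documents, so the size of the mixing cannot be computed.

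**6. The progression rule.** SHEAP 7.2 sets green at n ≥ 36 of 45. It is a count against target with no time element, and 45 of 45 meets it however the period is divided.

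**The case against.** The strongest reply is that the plan already shows randomisations month by month, so any reader can divide the series, as done above. That stands for randomisation, apart from November. It does not reach the referral, screening, eligibility and consent counts, which are the ones that answer research question 1.

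A second reply is that the added groups may be small and are partly visible: SHEAP 6.5 summarises age, service type with an inpatient category, and inpatient or outpatient status at baseline. If few such patients were screened, the pooled counts are close to what the narrower criteria would have given. That is possible. The documents do not give the numbers, and the baseline summaries cover only those who entered the trial.

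A reader might infer from the table in the working that the pooled rate understates recruitment under the current criteria. The documents do not support this:

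- The first months include start-up.
- Supplementary Table 12 also records staff turnover, leave and winter referral delays, which do not line up neatly with either period.
- The logged date may be a submission date. The table is headed as changes submitted for ethics approval, and the protocol's amendments section requires approval before anyone enters under revised procedures.

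Nor do the documents show that the recruitment figures fit neither set of criteria, because the contribution of the added routes is unknown. Planning the definitive trial only from the later months would discard a start-up period that a new trial may face as well. That choice is a matter of judgement, and the plan is not in error for leaving it open.

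**Conclusion.** The point holds as a minor one, in three parts.

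- **Average rate.** It is 3.25 per month over elapsed time against the stated 3, about 8% higher (15/13.86 = 1.08). This rests only on the stated dates and the total of 45. The 45/15 calculation is in the supplementary results text; the SHEAP does not prescribe it.
- **Objective 1 counts.** The percentage of eligible patients consenting pools two definitions of eligible. Direction and size are unknown.
- **CONSORT item 3b.** The N/A contradicts Supplementary Table 12.

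The before-and-after rates (0.7 to 1.9 against 3.9 to 4.4 per month) assume that 21/11/2022 was the date of effect. They describe the series and do not estimate an effect of the amendment. The recruitment progression result is unaffected.

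**What to change.** 1. In the text above Supplementary Table 1, compute the average over elapsed time (45 over 13.9 months, 3.25 per month), and say in SHEAP 7.2, Objective 1 that rates use elapsed time.
2. In SHEAP 6.1 to 6.3 and Objective 1, state the date on which the amendment took effect. Report referred, screened, eligible, consented and randomised counts before and after that date, with the numbers randomised aged 16-17 and from inpatient wards. Present these as description only, with a note that the early period includes start-up.
3. At CONSORT item 3b, replace N/A with the eligibility change and its reason.

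The cost is a few lines of wording and one extra table from dated screening records. Counts per period will be smaller and their intervals wider. Collection of demographics at screening was added by the same amendment, so an age-band split of patients screened earlier may be incomplete; the split by period needs only dates.
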